### **5 SAFETY AND ADVERSE EVENTS**

#### **5.1 ADVERSE EVENTS**

##### **5.1.1 Adverse Event (AE) Definition**

An AE is any untoward or unfavorable medical occurrence in a human subject, including any abnormal sign (e.g., abnormal physical exam or laboratory finding), symptom, or disease temporally associated with the use of study treatment, whether or not considered related to the study treatment.

### 5.1.2 Adverse Event Reporting in the Study Database

The following guidelines will be used to determine whether or not an adverse event is recorded in the study database.

Each adverse event will be graded according to the table for grading severity of adverse events (see **Appendix IV**).

Solicited adverse events will be recorded in the study database separately with data collection for 7 days after both the first vaccination and the second injection as detailed in Section 4.2.4; without the collection of attribution assessments. All unsolicited AEs will be recorded in the study database from receipt of first study injection through 28 days after each study injection. At other time periods between injections and after the second injection, only SAEs (as detailed in **Section 5.2**), new chronic medical conditions, and influenza or influenza-like illness will be recorded through the last study visit. However, cases of influenza or influenza-like illness will be recorded on an influenza endpoints form rather than on an adverse events form.

Any adverse events associated with licensed TIV that meet the criteria for reporting under the Vaccine Adverse Events Reporting System (VAERS) system, are the responsibility of the IoR to report in accordance with the guidance on reportable events available at the website <http://vaers.hhs.gov/professionals/index>. Refer to the brochure with description and guidance to the VAERS system, which is co-sponsored by the Centers for Disease Control and Prevention (CDC) and the Food and Drug Administration (FDA): [http://vaers.hhs.gov/resources/VAERS\\_Brochure.pdf](http://vaers.hhs.gov/resources/VAERS_Brochure.pdf).

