## 6.3 ENDPOINTS

### 6.3.1 Primary Endpoints: Safety

Assessment of product safety will include clinical observation and monitoring of hematological parameters. Safety will be closely monitored after each injection and evaluated by clinical visits through 24 weeks after the boost injection on each schedule. The following safety endpoints will be assessed for all Study Groups:

- Occurrence of solicited local reactogenicity signs and symptoms for 7 days following each vaccination
- Occurrence of solicited systemic reactogenicity signs and symptoms for 7 days following each vaccination
- Mean change from baseline for safety laboratory measures at week 3 and day of the boost
- Occurrence of adverse events of all severities through 28 days after the prime injection and through 28 days after TIV or ATIV boost
- Occurrence of serious adverse events through last study visit
- Occurrence of Influenza or influenza-like illness events through last study visit

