## **8.8 SAFETY MONITORING**

### **8.8.1 Protocol Safety Review Team**

Each site IoR is responsible for ensuring daily review of the site's clinical safety data as it becomes available. The Protocol Safety Review Team (PSRT) includes the Protocol Chair and/or Protocol Co-Chair, IND Sponsor Medical Officer, the UNI-CPSC Medical Monitor and each site IoR or designee. The PSRT will review the summary study safety data reports weekly until four weeks after the first study injections are administered to all subjects, and then monthly until 4 weeks after all subjects have completed the second study injections. The PSRT will be notified and convened to review any study pauses. The Protocol Chair, IND Sponsor Medical Officer, the UNI-CPSC Medical Monitor will continue to monitor the cumulative study safety data reports on at least a monthly basis through completion of the last study visit.

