
## **Appendix III: Schedule of Evaluations**

| SCHEDULE A                                                                                         |      |                 |                                                         |          |            |            |          |            |            |
|----------------------------------------------------------------------------------------------------|------|-----------------|---------------------------------------------------------|----------|------------|------------|----------|------------|------------|
|                                                                                                    |      | Screen          | VRC 703 Schedule of Evaluations for Group 1 and Group 2 |          |            |            |          |            |            |
| Visit                                                                                              |      | 01              | 02                                                      | 02A      | 03         | 05         | 05A      | 06         | 07         |
| Week of Study                                                                                      |      | -10 to 0        | W 0                                                     | W1       | W 3        | W 16       | W 17     | W19        | W 40       |
|  Day of Study                                                                          |      | -70 to 0        | D 0                                                     | D7       | D 21       | D112       | D119     | D 133      | D 280      |
| Clinical Evaluations                                                                               | Tube |                 |                                                         |          |            |            |          |            |            |
|  Informed Consent                                                                      |      | X               | X                                                       |          |            |            |          |            |            |
| Targeted physical exam for eligibility at screen; BP, pulse, temp, wt other visits; targeted exam. |      | X               | X                                                       |          | X          | X          |          | X          | X          |

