| Antibody assays and serum storage                                                                  | SST  | 16  | 24                                                      |          | 32         | 32         |          | 32         | 32         |
| PBMC and plasma for storage                                                                        | EDTA | 40  | 80                                                      |          | 60         | 60         |          | 60         | 60         |
| Daily Volume (mL)                                                                           |      | 63       | 107                                              | - | 95  | 92  | - | 92  | 92  |
| Max. Cumulative Volume (mL)                                                                 |      | 63       | 170                                              | - | 265 | 357 | - | 449 | 541 |

 Screening informed consent may be signed more than 8 weeks prior to study enrollment; screening evaluations may be repeated, if needed.

The screening blood draw for research does not need to be repeated if it was collected more than 70 days prior to enrollment. Day 0=day of enrollment and HA DNA vaccine injection. Day 0 evaluations prior to first injection are the baseline for assessing adverse events subsequently.

 Complete post vaccination evaluations (BP, pulse and injection site assessment) at 15-60 minutes after study injections.

 Negative pregnancy test results must be confirmed for women of reproductive potential prior to administering each injection. TIV is not contraindicated for pregnant women, but the woman must be informed of result prior to administering TIV as part of this research protocol. If pregnant, research blood draws will be one-fourth of shown volume or eliminated if the pregnant participant is anemic.

**Visit windows:** Schedule Visits 02A through 05 with respect to Day 0; the following visit windows apply: 02A(+4 days); Visits 03(+7 days); Visit 05 (+14 days). Schedule Visits 05A through 07 with respect to actual Visit 05 date; the following windows apply: 05A(+4 days); Visits 06 (+7 days), visit 07 (±7 day window). The schedule for Groups 1 and 2 does not include a “visit 04”.

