Storage samples of peripheral blood mononuclear cells (PBMCs) and serum collected during screening may be used for assay validation and site proficiency testing.

| SCHEDULE B                                                                                |      |                 |                                             |          |            |            |            |          |            |            |
|-------------------------------------------------------------------------------------------|------|-----------------|---------------------------------------------|----------|------------|------------|------------|----------|------------|------------|
|                                                                                           |      | Screen          | VRC 703 Schedule of Evaluations, Groups 3-6 |          |            |            |            |          |            |            |
| Visit                                                                                     |      | 01              | 02                                          | 02A      | 03         | 04         | 05         | 05A      | 06         | 07         |
| Week of Study                                                                             |      | -10 to 0        | W 0                                         | W1       | W 3        | W 16       | W 44       | W 45     | W47        | W 68       |
|  Day of Study                                                                 |      | -70 to 0        | D 0                                         | D7       | D 28       | D 112      | D 308      | D 315    | D 329      | D 476      |
| Clinical Evaluations                                                                      | Tube |                 |                                             |          |            |            |            |          |            |            |
|  Informed Consent                                                             |      | X               | X                                           |          |            |            |            |          |            |            |
| Physical exam for eligibility at screen; BP, pulse, temp, wt other visits; targeted exam. |      | X               | X                                           |          | X          | X          | X          |          | X          | X          |

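### AEs of all severities count through day 28 after each injection, but after at least 440 of 660 post-injection periods the last contact in that window is nominally day 21 and the next is months later

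*Protocol*

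**What the plan says.** Section 5.1.2 sets the collection rule: "All unsolicited AEs will be recorded in the study database from receipt of first study injection through 28 days after each study injection". Outside those periods the database takes much less: "At other time periods between injections and after the second injection, only SAEs", new chronic medical conditions, and influenza or influenza-like illness. Section 6.3.1 lists as a primary safety endpoint "Occurrence of adverse events of all severities through 28 days after the prime injection and through 28 days after TIV or ATIV boost".

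Appendix III supplies the contacts. Each injection is followed by a telephone contact at about one week and a clinic visit at about three weeks (Visit 03 after the prime, Visit 06 after the boost). The next contact after that is at week 16 following the prime, and 24 weeks after the boost following the boost. From Visit 03 onward, Schedule A (Groups 1-2) prints the days as "D 21 | D112 | D119 | D 133 | D 280". For Schedule B (Groups 3-6) the week row reads "W 3 | W 16 | W 44 | W 45 | W47 | W 68" and the day row "D 28 | D 112 | D 308 | D 315 | D 329 | D 476". In both schedules Visit 03 may be up to 7 days late, and the post-boost windows read "Visits 06 (+7 days), visit 07 (±7 day window". Interim AE history is taken at every clinic visit after enrollment.

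**The concern.** The endpoint window is a week longer than the nominal schedule of contacts that feeds it. A subject seen on the target day has days 22 to 28 still ahead. The protocol schedules no further enquiry until months later, when minor events are easily forgotten or misdated. A subject seen a week late in the same window has the full 28 days covered. Ascertainment of a primary safety endpoint therefore depends on when the appointment happened to fall. Section 4.2.6 keeps changes in concomitant medication out of the database, with narrow exceptions, so they give little cross-check on later recall.

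What is at stake is the completeness and evenness of the counts of mild and moderate non-serious AEs in the last week of the window.

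**Working it through.** **Inputs.** The 28-day window is from sections 5.1.2 and 6.3.1. Visit weeks, days and windows are from Appendix III, Schedules A and B. Numbers of subjects are from section 6.4: 110 in Groups 1-2 and 220 in Groups 3-6.

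**Step 1: do the printed days reproduce (day = 7 × week)?**
- Schedule A: weeks 0, 1, 3, 16, 17, 19, 40 give days 0, 7, 21, 112, 119, 133, 280. All agree.
- Schedule B: weeks 0, 1, 16, 44, 45, 47, 68 give days 0, 7, 112, 308, 315, 329, 476. All agree.
- Schedule B, Visit 03: 7 × 3 = 21, but 28 is printed. This is the only mismatch.

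**Step 2: last contact inside the 28-day window, at nominal days.**
- Groups 1-2 prime: D21.
- Groups 1-2 boost: 133 − 112 = 21 days after the boost.
- Groups 3-6 boost: 329 − 308 = 21 days after the boost.
- Groups 3-6 prime: day 21 if W 3 is right, day 28 if D 28 is right.

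**Step 3: delay until days 22 to 28 are next asked about.** The next contact after the prime is D112. After the boost it is 280 − 112 = 168 days (Schedule A) or 476 − 308 = 168 days (Schedule B).

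| Period | Next contact, days after injection | Delay from day 28 | Delay from day 22 | Range using the next visit's window |
|---|---|---|---|---|
| Groups 1-2 prime | 112 (+14) | 112 − 28 = 84 | 112 − 22 = 90 | 84 to 104 |
| Groups 3-6 prime, if W 3 | 112 (±7) | 84 | 90 | 77 to 97 |
| All boosts | 168 (±7) | 168 − 28 = 140 | 168 − 22 = 146 | 133 to 153 |

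In weeks, the nominal delays are 12.0 to 12.9 after the prime and 20.0 to 20.9 after the boost.

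**Step 4: how many periods are affected.** There are 330 × 2 = 660 planned post-injection periods, counting the concurrent Day 0 injections in Groups 5 and 6 as one. The gap is unambiguous at nominal days for 110 primes + 330 boosts = 440, or 440/660 = 67%. The remaining 220 (33%) are the Group 3-6 primes, which turn on the W 3/D 28 conflict.

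**Step 5: uncovered days per subject.** With the visit on day v, uncovered days = 28 − v. The +7-day window allows v = 21 to 28, so the gap runs from 7 days (7/28 = 25% of the window) down to 0. If Schedule B Visit 03 is D 28 (+7), it falls on days 28 to 35 and the gap is 0.

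**Step 6: which Schedule B reading fits the rest of the protocol.** Sections 3.1 and 6.3.2 put the primary HAI measurement in Groups 3 and 4 at 3 weeks after the prime, and every other printed day equals 7 × week. Both favour W 3. The printed D 28 nevertheless stands in the current text and needs a decision.

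**The case against.** The strongest reply is that the endpoint can still be collected. Every later clinic visit takes an interim AE history. Section 4.2.4 asks subjects to contact the clinic about concerning symptoms, with no stated end date. Late-window visits cover some or all of days 22 to 28. SAEs, new chronic conditions and influenza run to the last visit. All of this stands, and it confines the problem to non-serious events that a subject would not think worth a call. It does not remove the problem, because the endpoint counts every severity.

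Four stronger readings are tempting, and the documents do not support them.

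- **That no injection has a day-28 contact.** As printed, Schedule B Visit 03 is D 28, so this cannot be asserted for the Group 3-6 primes.
- **That a quarter of the window is lost, or a definite share of events.** The 25% is the maximum for a subject seen on day 21. Multiplying it by an assumed forgetting rate of, say, 30% to 70% gives 7.5% to 17.5%. Neither the forgetting rate nor even onset over 28 days comes from the protocol, and the product ignores late-window visits.
- **That a planned comparison is biased.** The delay is longer after the boost than after the prime, but no prime-versus-boost AE comparison is planned. Section 6.5.3 tabulates AEs, and section 6.4 disclaims a formal hypothesis test. Groups randomized together share one schedule. The uneven delay matters only to a reader who sets prime and boost tables, or Groups 1-2 and Groups 3-6, side by side.
- **That safety oversight ends too early.** Section 8.8.1 has the full review team meet weekly "and then monthly until 4 weeks after all subjects have completed the second study injections", so a Group 3-6 post-boost event on days 22 to 28 could surface after its last scheduled review. The same section keeps the Protocol Chair, the sponsor's medical officer and the medical monitor reviewing at least monthly to the last visit. The pause rule (section 4.5) concerns related Grade 4 or 5 events, and it does not rest on recall of mild ones.

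**Conclusion.** The point holds in a limited form. The 28-day all-severity window outlasts the nominal three-week visit in 440 of 660 post-injection periods, and in all 660 if W 3 is the right reading of Schedule B. Between 0 and 7 days per subject are uncovered, depending on appointment timing. The next scheduled enquiry comes 84 to 90 days (prime) or 140 to 146 days (boost) after days 28 to 22. The expected consequence is uneven under-reporting of mild or moderate non-serious AEs. Its size cannot be derived from the document.

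The calendar arithmetic assumes only the printed nominal days and windows. That events will be under-reported is a judgement about recall over 12 to 21 weeks. The W 3/D 28 conflict is a plain internal inconsistency. If both entries were followed as printed, post-prime coverage would also differ between Groups 1-2 (day 21) and Groups 3-6 (day 28).

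**What to change.** 1. Reconcile the week and day rows for Visit 03 in Schedule B, and check the result against the 3-week HAI endpoint.
2. Add to both schedules a brief telephone AE contact at day 28 (+4 days) after each injection, for any subject whose Visit 03 or Visit 06 took place before day 28. It can follow the format of the existing telephone contacts at Visits 02A and 05A. The cost is at most 330 × 2 = 660 short calls by existing site staff, and fewer to the extent that visits fall on day 28 or later.
3. If calls are not feasible, keep the 28-day collection, also tabulate AEs through day 21 as the window ascertained uniformly, and state that days 22 to 28 are incompletely ascertained. This costs one extra table and a sentence.

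Simply shortening the endpoint to 21 days is the weaker choice, because it would discard events on days 22 to 28 that late-window visits already capture.

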## 5.2 **SERIOUS ADVERSE EVENTS**

### 5.2.1 Serious Adverse Event Definition

The term “Serious Adverse Event” (SAE) is defined in the 21 CFR 312.32 in terms of the following outcomes: Death, a life-threatening adverse event, inpatient hospitalization or prolongation of existing hospitalization, a persistent or significant incapacity or substantial disruption of the ability to conduct normal life functions, or a congenital anomaly/birth defect. Important medical events that may not result in death, be life-threatening, or require hospitalization may be considered serious when, based upon appropriate medical judgment, they may jeopardize the patient or subject and may require medical or surgical intervention to prevent one of the outcomes listed in this definition. Examples of such medical events include allergic bronchospasm requiring intensive treatment in an emergency room or at home, blood dyscrasias or convulsions that do not result in inpatient hospitalization, or the development of drug dependency or drug abuse.”

An SAE will be considered "life-threatening" if, in the view of either the investigator or sponsor, its occurrence places the patient or subject at immediate risk of death. It does not include an adverse event or suspected adverse reaction that, had it occurred in a more severe form, might have caused death.

### 5.2.2 Reporting Serious Adverse Events to the IND Sponsor

Adverse events that meet Serious Adverse Event (SAE) Reporting Requirements must be reported and submitted by the clinical site on an expedited basis to the IND sponsor, VRC/NIAID/NIH, according to sponsor guidelines as follows:

- death
- life-threatening
- results in persistent or significant disability/incapacity
- requires unplanned inpatient hospitalization or prolongation of existing hospitalization
- is a congenital anomaly/birth defect in the offspring of a study subject
- is an important medical event that may jeopardize the patient or may require intervention to prevent one of the other outcomes listed above.

In addition, any event, regardless of severity, which in the judgment of a site investigator represents a serious adverse event, may be reported on an expedited basis.

A site investigator will communicate an initial SAE report within 24 hours of site awareness of occurrence to VRC (IND Sponsor) through the communication methods provided by the Data Coordinating Center, EMMES Corporation (Rockville, MD).

Any SAE entered into the study database will generate automatic email notification to the UNI-CPSC Medical Monitor and VRC Medical Officer. This or a written report by the study site sent to the attention of the UNI-CPSC Medical Monitor (Email: [[contact]](mailto:[contact]) or [contact]) must be submitted within 3 working days in order for the sponsor to comply with regulations mandating sponsor notification of specified SAEs to the FDA within 7 calendar days.

The investigator must submit additional information as it becomes available.

#### 5.2.3 IND Sponsor Reporting to the FDA

It is the responsibility of the IND Sponsor to make the determination of which SAEs are “serious and unexpected suspected adverse reactions” (SUSARs) as defined in 21 CFR 312.32.

- *Suspected adverse reaction* means any adverse event for which there is a reasonable possibility that the drug caused the adverse event.
- *Unexpected Adverse Event* means an AE that is not listed in the Investigator’s Brochure or is not listed at the specificity or severity that has been observed.

All SUSARs, as determined by the IND Sponsor, will be reported to the FDA as IND Safety Reports and IND Safety Reports will be provided to all participating Investigators by the UNI-CPSC.

The IND Sponsor will also submit an IND Annual Report of the progress of the investigation to the FDA as defined in 21 CFR 312.33.

### 5.3 **REPORTING TO SITE IRBs**

Each site IoR is responsible for reporting adverse events to the site IRB in accordance with their IRB’s requirements for expedited reporting and continuing review reporting.

Site-specific data reports will be made available to facilitate this continuing review reporting. If there is an IND Safety Report, these will be provided to all sites with instruction as to whether or not any actions need to be taken, such as amendment of consent. Investigators must maintain documentation of compliance with actions required for IND safety reports.

